## Abstract

**Background:**

As the coronavirus disease 2019 (COVID-19) pandemic has spread globally, its sequelae, called Long COVID, have persisted, troubling patients worldwide. Although fatigue is known to be the most frequent among Long COVID symptoms, its mechanism and treatment have not been clearly demonstrated. In 2022, we conducted a preliminary prospective case series and found that acupuncture and moxibustion were feasible interventions for fatigue. This study is a pilot patient-assessor-blinded randomized sham-controlled trial to evaluate the efficacy and safety of acupuncture treatment for patients with fatigue that has persisted for at least 4 weeks after recovery from COVID-19.

**Methods:**

Thirty patients will be recruited and randomly assigned to either the acupuncture or sham acupuncture treatment groups. Treatment will be conducted thrice a week for both groups during 4 weeks. The primary outcome will be the efficacy and safety of acupuncture, including numeric rating scale (NRS), brief fatigue inventory (BFI), fatigue severity scale (FSS), and adverse event evaluation. Secondary outcomes will be evaluation of improvement in the comorbid symptoms of fatigue and feasibility variables. Outcome variables will be assessed before treatment, 4 weeks after treatment, and 8 weeks after treatment completion.

**Discussion:**

The results of this study will be used to clarify the efficacy and safety of acupuncture treatment for persistent fatigue in patients with Long COVID. Additionally, the feasibility of the study design was validated to provide evidence for future full-scale randomized controlled trials.

**Clinical trial registration**: identifier: KCT0008656 https://cris.nih.go.kr/cris/search/detailSearch.do?seq=24785&search_page=L.

## Introduction

Long COVID manifests as a wide range of newly developed symptoms that persist after initial acute SARS-CoV-2 infection (1). While the COVID-19 pandemic has lasted for more than 2 years, most symptoms of the acute phase have become mild or even asymptomatic, but its long-term consequences persist for months or longer (2). Although survivors must return to society after recovering from COVID-19, their ongoing health problems impair their quality of life and ability to work in the absence of standardized treatment. These prolonged implications remain a global public health burden rather than COVID-19 itself (3).

Among more than fifty known post-COVID conditions, fatigue has been reported as the most common symptom, affecting 58% of patients with Long COVID (4). Long COVID fatigue is defined as the decrease in physical and/or mental performance that results from changes in central, psychological, and/or peripheral factors, which is different from objective fatigability (5). It occurs more in women significantly and is usually accompanied with fatigue-related symptoms such as stress, anxiety, depression and cognitive impairment (6, 7). Its pathophysiology remains unknown, and several clinical recommendations suggest temporary self-management and multidisciplinary rehabilitation for its treatment (8). Although fatigue symptoms reduce daily activity, motivation, and concentration, the fact that patients must vaguely endure fatigue without reliable treatment interventions has increased their anxiety. Therefore, complementary and alternative medicine (CAM) interventions have been sought as treatment and management strategies (9).

Acupuncture is a potential intervention for fatigue in patients with Long COVID (10). Acupuncture has been demonstrated to be an effective and safe modality for cancer-related fatigue and chronic fatigue syndrome by alleviating neuroinflammatory response, modulating immune responses, regulating neuropeptides (e.g., dopamine, *β*-endorphin), promoting oligodendrocyte proliferation and stimulating NO production (11–13). Although it has been used practically for fatigue symptoms in other diseases, only a few case studies have explored the possible application of acupuncture treatment for persistent fatigue following COVID-19 (14).

In 2022, our research team will complete a preliminary case series study to assess the feasibility of acupuncture and moxibustion treatment for several Long COVID symptoms. In this case series, all 16 participants complained of multiple symptoms, such as fatigue, olfactory disturbance, joint pain, and alopecia after COVID-19 infection. Because fatigue was assessed as the most severe symptom, the subjects expected to be treated mostly for this. The participants ended up seeking CAM interventions, such as acupuncture or moxibustion treatment, as the specific cause could not be determined even after testing at a tertiary general hospital, and there was no dependable treatment for postviral fatigue. After 12 treatment sessions, we confirmed a significant improvement in fatigue, which persisted even after 4 weeks of follow-up evaluation. In addition, there were no severe adverse events, except for a few mild blisters after moxibustion treatment.

To our knowledge, no randomized sham-controlled trial (RCT) has evaluated the efficacy and safety of acupuncture for treating fatigue after COVID-19. Therefore, we designed a pilot RCT based on our previous prospective case study to assess the efficacy and safety of acupuncture for fatigue after COVID-19 infection compared with a control group treated with non-penetrating sham acupuncture because of its physiologically inert characteristics.

## Study objectives

The aims of this pilot RCT will be as follows: (1) to test the efficacy and safety of acupuncture treatment for patients experiencing persistent fatigue after recovery from COVID-19 and (2) to explore the feasibility of future full-scale RCT.

## Materials and methods

This protocol followed the Standard Protocol Items: Recommendations for Interventional Trials (SPIRIT) (Supplement 1) (15). The trial was listed on the Clinical Research Information Service (CRIS) registry with study ID KCT0008656 in July 2023.

### Trial design and setting

A two-arm, randomized, patient-assessor-blinded, sham-controlled trial will be conducted at the Kyung Hee University Korean Medicine Hospital in Seoul, Korea. This study was approved by the Institutional Review Board (IRB) of Kyung Hee University Korean Medicine Hospital (KOMCIRB 2023-04-006-001). Thirty participants will be recruited through subway advertisements and posters. Patient enrollment will begin in August 2023 and is expected to end in November 2023. Eligible and consenting patients will be randomly allocated to either the verum acupuncture or the sham acupuncture group at a ratio of 1:1. All subjects will receive twelve sessions of treatment for 4 weeks and will be assessed at baseline, week 4, and week 12. The trial design is summarized in Figure 1. Figure 2 outlines the SPIRIT schedule for enrollment, interventions, and assessments.

**Figure 1 fig1:**
[figure not shown]
Flow chart of study.

**Figure 2 fig2:**
[figure not shown]
SPIRIT schedule of enrollment, interventions, and assessments. *SPIRIT, standard protocol items: recommendations for interventional trials; NRS, numeric rating scale; BFI, brief fatigue inventory; FSS, fatigue severity scale; AEs, adverse events; EQ-5D-5L, euroQol-5-dimension 5 level; ISI-K, korean-validated version of the insomnia severity index; WIWI, Was It Worth It questionnaire.

### Participants

A formal sample size calculation was not performed because this was designed as a pilot study to calculate the appropriate sample size for subsequent RCTs. Our study will recruit 30 patients, based on previous studies that recommended the minimum number of people necessary for preliminary research in the field of life sciences to be 10 to 35, considering a 20% drop-out (16–18).

Participants who have the following conditions will be included: (1) aged 20 to 65 years; (2) diagnosed with COVID-19 and quarantined (and cured) at least 1 month ago; (3) experiencing newly developed fatigue that has persisted for more than 4 weeks after being cured of COVID-19, and whose symptom intensity is 4 or higher on the 0–10 numeric rating scale (NRS); and (4) voluntarily agreeing to participate in the study through a written consent form after listening to the purpose and characteristics of this clinical study.

Participants who have one or more of the following conditions will be excluded: (1) having history of diseases (cancer, anemia, hypothyroidism or psychiatric disease such as depression) or surgical operation that can cause fatigue symptom before the infection of COVID-19; (2) having fear of acupuncture treatment; (3) pregnant, breast feeding or expecting a pregnancy during the study period; (4) judged to find it difficult to comply with this treatment protocol (e.g., visiting the hospital, or filling in a questionnaire); (5) participating in another clinical study; (6) with other factors deeming them inadequate for participation in the view of research investigators.

Eligible patients will be informed of the aims and potential benefits, risks, alternatives, and responsibilities of the study by a Korean Medicine (KM) doctor throughout the consent process and written consent will be obtained. The patients’ information will remain confidential, and they will have the right to withdraw without prejudice at any time.

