### Randomization and blinding

Randomization will be performed by an independent statistician using a computerized randomization with R package (R Version 4.3.1, Windows) with 1:1 allocation ratio. Prior to randomization, the study coordinator will ensure that each participant met the inclusion and exclusion criteria and informed consent is obtained. Random allocation will be conducted by an independent study coordinator, who will open the corresponding envelope in front of the participant.

The participants, outcome assessors, and statisticians will be blinded to the allocation, whereas practitioners will not. To evaluate the blinding, patients will assess their allocation guess and credibility rating immediately after the last treatment session.

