### Statistical analysis

Statistical analyses will be performed on both an intention-to-treat (ITT) basis and per-protocol (PP) population (95% confidence interval [CI]) using the SAS package program (Version 9.4; SAS Institute Inc., United States). Missing data will be replaced according to the last observation carried forward (LOCF) method. Baseline characteristics will be shown as mean ± standard deviation (SD) for continuous data and n (%) for categorical data. To analyze the baseline characteristics, we will conduct between-group comparisons at baseline using two-sample *t*-test or Wilcoxon rank sum test for continuous data and chi-squared test or Fisher’s exact test for categorical data with *p* < 0.05, as statistically significant, to determine whether the data are normally distributed.

For primary and secondary outcome measures, the mean difference from the baseline values to the end of treatment in each group will be compared using a two-sample *t*-test or Wilcoxon rank-sum test. If we needed to compare repeated measures, we would implement the repeated measures ANOVA. If any imbalances in baseline characteristics between groups were encountered, we will conduct analysis of covariance (ANCOVA) using these variables as covariates and the randomized group as a fixed factor. We might conduct subgroup analysis according to the baseline demographics, such as analysis on symptom duration over or under than 3-month period. In addition, to compare pre and post treatment assessment, we would use paired *t*-test, after evaluating the normality of the data. The safety and feasibility variables are descriptively presented with detailed explanations. Blinding assessment will be analyzed using Bang’s blinding index (29).

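### Symptom duration can differ between two arms of 15 by chance, and the main comparison adjusts for it only if an imbalance is noticed; it should always be in the model

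*Protocol article*

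**What the plan says.** All references are to the protocol article.

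- **Participants.** Both time criteria are lower bounds: "diagnosed with COVID-19 and quarantined (and cured) at least 1 month ago" and "newly developed fatigue that has persisted for more than 4 weeks after being cured of COVID-19". No upper bound is given.
- **Participants, sample size.** "Our study will recruit 30 patients", and "A formal sample size calculation was not performed because this was designed as a pilot study".
- **Randomization and blinding.** Allocation is done "using a computerized randomization with R package (R Version 4.3.1, Windows) with 1:1 allocation ratio". No stratification or minimisation factor is named. Practitioners know the allocation.
- **Statistical analysis.** Change from baseline to the end of treatment is compared between groups by a two-sample t-test or rank-sum test. ANCOVA is planned only where a baseline imbalance turns up, with the imbalanced variables as covariates. Baseline characteristics are themselves tested at p < 0.05. Duration is named once: "We might conduct subgroup analysis according to the baseline demographics, such as analysis on symptom duration over or under than 3-month period".
- **Study objectives and Discussion.** Efficacy is part of the first aim, and the data are to feed the sample size calculation of the full-scale trial.

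**The concern.** A patient about 5 weeks after recovery and a patient with fatigue for two years can both enrol. If they differ in natural course, duration is a prognostic factor. The authors' own example of a subgroup suggests they think it may matter.

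In a trial of 30, such a factor can easily fall unevenly between the arms. The plan then relies on two weak provisions. One is an adjustment triggered by an imbalance. The other is a subgroup analysis that may or may not be done, on cells of about 7 or 8 at best.

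Two things are at stake. The estimate from this one trial could be shifted in either direction. And residual variation due to duration would lower precision and raise the SD used to plan the next trial.

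**Working it through.** **Inputs from the article.** N = 30, allocated 1:1, taken as 15 per arm; 3-month duration cut; p < 0.05 for baseline tests. The article gives no effect size, SD or power behind N = 30, so there is no planned figure to reproduce.

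**Assumptions, not in the article.** Recent-onset share (up to 3 months) 20% to 50%; extra natural improvement in recent-onset patients D = 1 to 3 NRS points by the end of treatment; SD of NRS change within a duration group 2; two-sided 5% test; true effect 0 or 2 points.

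**Step 1: chance of imbalance.** With K recent-onset patients among 30, the number X in one arm is hypergeometric: P(X = x) = C(K, x) · C(30 − K, 15 − x) / C(30, 15). The gap between arms is |2X − K|.

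| Share (K) | Smallest gap of 3 or more | Probability |
|---|---|---|
| 20% (6) | 5 v 1 | 17% |
| 30% (9) | 6 v 3 | 43% |
| 40% (12) | 8 v 4 | 26% |
| 50% (15) | 9 v 6 | 47% |

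The series is uneven because an even K allows only even gaps. For K = 15, P(7 or 8) = 2 × 6435² / 155117520 = 0.534, so P(gap ≥ 3) = 0.466. Subtracting P(6 or 9) = 2 × 5005² / 155117520 = 0.323 gives P(gap ≥ 5, that is 10 v 5 or worse) = 0.143.

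**Step 2: would the imbalance rule react?** The article does not define when an imbalance counts as encountered; its p < 0.05 baseline test is the natural reading. For 10 v 5, Fisher's exact p is 0.143. The uncorrected chi-squared statistic is 30 × (10 × 10 − 5 × 5)² / 15⁴ = 3.33, p about 0.07. Neither reacts. Fisher's test needs 11 v 4 at a 50% share, 10 v 2 at 40% and 8 v 1 at 30%. Across those shares it flags 0.8% to 2.7% of trials, and chi-squared flags 3% to 11%.

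**Step 3: shift in one trial's estimate.** Shift = D × gap / 15.

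- 9 v 6: 3/15 × (1, 2, 3) = 0.2, 0.4, 0.6 points.
- 10 v 5: 5/15 × (1, 2, 3) = 0.33, 0.67, 1.0 points.

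For scale, the standard error of the difference is 2 × √(2/15) = 0.73.

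**Step 4: error rate and power.** Simulation, 8,000 trials per setting, 50% share, SD 2. With no true effect, the unadjusted test rejects in 4.9% to 5.4% of all trials. Within trials split 10 v 5 or worse it rejects in about 8%, 11% and 18% for D = 1, 2, 3; ANCOVA on duration brings this to about 4% to 6%. Power for a true effect of 2 points:

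| D | Unadjusted | ANCOVA on duration | Stratified + ANCOVA |
|---|---|---|---|
| 0 | 76% | 75% | 76% |
| 1 | 73% | 73% | 75% |
| 2 | 65% | 74% | 76% |
| 3 | 56% | 74% | 75% |

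**Step 5: SD passed on.** With a 50/50 mix the variance is 2² + D²/4. For D = 1, 2, 3 this is 4.25, 5 and 6.25 instead of 4. Required sample size is proportional to variance, so the next trial would need about 6%, 25% or 56% more patients than with an adjusted analysis.

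**The case against.** A reader might infer that natural recovery would bias this trial, so that it passes for an acupuncture effect. The document does not support that. A concurrent randomised sham arm shares whatever recovery occurs, and the overall false-positive rate is near 5% without any adjustment. A spurious difference arises only given a realised imbalance, and the test's overall error rate already allows for that. This part of the objection stands in full.

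Other points also have force:

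- **The premise is assumed.** Nothing in the article says that short-duration fatigue resolves faster. The Introduction's remark that "its long-term consequences persist for months or longer" does not show it. The 3-month split is offered only as an example.
- **The window is short.** The main comparison ends with the 4-week treatment period, so the assumed 1 to 3 points must arise within that time and not over the whole follow-up. The upper end may be generous.
- **The frequent splits have small effects.** The 47% event starts at 9 v 6, a shift of 0.4 points at D = 2, and even 0.67 is below one standard error.
- **The plan is not silent.** It commits to ANCOVA when an imbalance is encountered. That reply is only partial: the trigger is undefined, duration is not named as a covariate, and a p < 0.05 rule would miss a 10 v 5 split.
- **A condensed article may omit detail.** One could read it as saying that duration is excluded from allocation; it says only that allocation is computerised 1:1. The analysis text, however, is explicit about how duration is handled, and the point rests on that.
- **It is a pilot.** The article acknowledges the small sample. Efficacy is nevertheless a stated aim, and the data are to be used for planning.

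**Conclusion.** The point holds as a matter of precision and of a badly fixed adjustment rule, and not as a claim of systematic bias. An appreciable gap in recent-onset patients is fairly likely (17% to 47% for a gap of 3 or more), and the conditional rule would seldom act on it.

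If duration is worth 2 NRS points, always adjusting raises power from about 65% to 74%, and a 10 v 5 split no longer shifts the estimate by 0.67 points. If it is worth 1 point, the power gain is negligible. If it is worth nothing, the covariate costs about one percentage point of power. These sizes rest on the assumed SD of 2, the 50% share and the assumed range for D, none of which the article gives.

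A reader might also infer that eligibility needs a maximum duration. It does not: the difficulty is met in the analysis, with the population as defined. The change is modest in importance and close to free.

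**What to change.** In Statistical analysis, replace the imbalance-triggered adjustment for this factor by a between-group ANCOVA that always includes symptom duration at entry, coded as up to 3 months v over 3 months. Present results in the two duration groups descriptively instead of as an optional tested subgroup. Carry the residual SD from this model into the full-scale sample size if that trial will adjust in the same way.

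The cost is one degree of freedom. The duration value is already needed for the subgroup split the plan mentions.

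Optionally, stratify the allocation list by the same cut, with block sizes varied and concealed because practitioners are unblinded. This means two lists and two envelope sets. The further gain is small (about 74% to 76% power at D = 2), though it also prevents very unequal duration groups between arms. The downsides are slightly unequal arm sizes from incomplete blocks and some predictability of allocation.

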### Randomization and blinding

Randomization will be performed by an independent statistician using a computerized randomization with R package (R Version 4.3.1, Windows) with 1:1 allocation ratio. Prior to randomization, the study coordinator will ensure that each participant met the inclusion and exclusion criteria and informed consent is obtained. Random allocation will be conducted by an independent study coordinator, who will open the corresponding envelope in front of the participant.

The participants, outcome assessors, and statisticians will be blinded to the allocation, whereas practitioners will not. To evaluate the blinding, patients will assess their allocation guess and credibility rating immediately after the last treatment session.

### Intervention

Reporting of intervention in this protocol followed the Standards for Reporting Interventions in Clinical Trials of Acupuncture (STRICTA) guidelines (Supplement 2) (19). Acupuncture treatment will be performed by certified practitioners with at least 6 years of KM education and more than 2 years of clinical experience. Regardless of their allocation, all participants will be treated for a total of 12 sessions (three times per week for 4 weeks) in a similar environment to a KM hospital setting with a blinding curtain (Supplement 3). The standard operating procedure (SOP) will be developed by the principal investigator and co-investigators, and acupuncture practitioners will be required to attend a training course on standardized treatment before the beginning of the study.

### Verum acupuncture treatment

Fixed acupuncture will be provided to patients in the verum acupuncture treatment group. The acupuncture points were selected according to the consensus of board-certified professional KM doctors based on a textbook, literature review, and the points used in our previous prospective case series study (20–22). Ten acupuncture points were chosen: CV12, CV4, bilateral LI4, SP6, ST36, and LI11, in accordance with the WHO Standard Acupuncture Point Locations (Table 1).

**Table 1 tab1:** Acupuncture point locations.

Acupuncture point	Location
CV12	On the upper abdomen, 4 cun superior to the center of the umbilicus, on the anterior median line.
CV4	On the lower abdomen, 3 cun inferior to the center of the umbilicus, on the anterior median line.
LI4	On the dorsum of the hand, radial to the midpoint of the second metacarpal bone.
SP6	On the tibial aspect of the leg, posterior to the medial border of the tibia, 3 cun superior to the prominence of the medial malleolus.
ST36	On the anterior aspect of the leg, on the line connecting ST35 with ST41, 3 cun inferior to ST35.
LI11	On the lateral aspect of the elbow, at the midpoint of the line connecting LU5 with the lateral epicondyle of the humerus.

For patient blinding, the Park Sham Acupuncture Device (Dong Bang Acuprime, United Kingdom) will be attached to the acupuncture points using double-sided tape. Sterilized disposable 25 mm × 40 mm acupuncture needles (Dong Bang, South Korea) will be used at a depth of 5–20 mm, depending on the anatomical location of the acupuncture point. After insertion, needles will be twisted several times until the participants feel “de qi” sensation and be left for 20 min. Infrared therapy will be administered to the abdomen during needle retention.

### Sham acupuncture treatment group

For the sham acupuncture treatment group, 25 mm × 45 mm-size non-penetrating needles devised by Park et al. (Acuprime, United Kingdom) will be used (23, 24). These are sterilized disposable blunt needles that only contact the skin without penetration and will be propped by a validated guiding tube called the Park Sham Acupuncture Device (Dong Bang Acuprime, UK) which will be attached to the same acupuncture points as those of the verum acupuncture group. There will be no manipulation of qi, and the needles will be retained for 20 min.

